## Background

Falls are a leading cause of death and disability among older adults [1]. About one third of people aged 65 years or older fall at least once a year [1, 2]. In 2013, Australia had 14 % of its population aged 65 years and over [3] with approximately 10 % have multiple falls [4] and 20 % of those who fall experience injuries requiring medical attention [2]. In 2011–12, there were 88,386 fall related hospitalisations in Australia for people aged over 65 years, with the most common injury being hip or other lower limb fracture [5]. Hip fractures in particular are associated with high level of mortality and morbidity, with recent studies reporting that 20 % of hip fracture patients die within 12 months of injury [6], and over half do not regain pre-fracture mobility or large muscle group abilities up to two years after the fracture [7].

Most falls are associated with one or more identifiable risk factors [8] and the risk of falling has a direct association with the number of risk factors involved [9]. Physiological factors, such as lower extremity muscle weakness, gait and balance impairments and functional impairments, have been highly associated with the risk of falls and are most often targeted by preventive programmes [9]. Therefore, targeting these modifiable risk factors through exercise programmes seems to be a suitable way to reduce the risk of falls [2, 10].

Exercise programmes have been shown to be effective in reducing the risk of falling and the rate of falls [10] as they can improve muscle strength, flexibility, balance, coordination, proprioception, reaction time and gait [11]. These positive outcomes have been observed even in the very old and frail [11]. A meta-analysis identified that 50 h cumulative exercise (irrespective of exercise frequency) is needed to reduce the risk of falls [12]. A recent telephone survey applied in NSW has shown that older people’s participation to strength or balance-challenging activities was 21.0 % (95 % CI: 9.8–22.2) with only 5.3 % participating in both forms (strength and balance-challenging activities) [13]. Thus, there is a need to improve long-term participation in physical activity, which is not a common habit for most older individuals [14].

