### Participants

One hundred and twenty older people living in the community aged between 60 and 90 years old who have had one or more falls in the previous 12 months or who are concerned about having a fall will be recruited. Participants who are generally active and independent in the community with no more than a single point stick used for regular outdoors walking (at least three times per week) will be included. The aim in these inclusion criteria is to target those with mild falls risk, but who remain relatively active, using a health promotion and prevention approach.

Older adults will be excluded from this study if they have: 1) any uncontrolled non-musculoskeletal conditions that would make testing difficult and uncomfortable, such as chronic obstructive airways disease and congestive heart failure; 2) a pre-existing neurological or orthopaedic condition that affects lower limb strength (e.g.: polio, stroke); 3) any of the following foot conditions: partial foot amputation or ulceration or foot fractures; 4) any uncontrolled musculoskeletal conditions that may affect ambulation (rheumatoid arthritis, gout, etc.). Participants with heart problems (e.g. chest pain (angina), heart murmur, heart rhythm disturbance, heart valve disease or heart failure) will be required to obtain a medical clearance from their general practitioner in order to participate in this study. Participants with any documented medical condition or physical impairment that is judged by the medical practitioner to contraindicate their inclusion will be excluded. Written informed consent will be sought from the participants

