
#### Secondary measures

The following functional tasks and psychosocial variables will be assessed:Hand grip strength test [31] will be used to measure muscle strength. Hand-grip strength is a simple, reliable, inexpensive surrogate of overall muscle strength and a valid predictor of physical disability and mobility limitation [32]. Using a TTM digital hand dynamometer (Mentone Educational Centre, Melbourne, VIC), participants will be asked to perform two maximum force trials with each hand and the best score of two attempts will be recorded. Participant will be seated on a 43 cm high chair, feet flat on the floor, with shoulder adducted and neutrally rotated, elbow flexed at 90° and forearm in neutral and the wrist between 0 and 30° extension and between 0° and 15° ulnar deviation [33]. The maximum values of the left- and right-hand grip measurements will be summed and be used for the analysis to remove consideration of hand dominance [31].Two minute walk test will be used to assess exercise tolerance [34] and functional mobility [35]. Improvement in distance walked within the test interval is attributed to improvement in cardiac output, in mechanics of ventilation, or in muscular conditioning [36]. Participants will be asked to walk for 2 min on a demarcated area at a comfortable pace and the maximum distance achieved will be recorded. Participant will be allowed to use their gait aid if regularly used for indoors walking.Lower limb strength will be assessed via the sit-to-stand test [37] and measurement of the strength of the knee extensor muscles using a purposely built force transducer [38]. The sit to stand test is a simple test used to measure mobility and lower limb strength [37] and is also included in fall risk assessments [39, 40]. Participants will be asked to stand from a 43 cm high chair as many times as possible for a period of 30 s without any assistance of the assessor. Participants will be asked if they need their hands to assist them in standing up from the chair and this information will be recorded for further analysis. Otherwise, arms will be kept to the side of their body during the test.The strength of the knee extensor muscles of both limbs will be measured with a purposely built force transducer which will be attached to the participant’s leg using a webbing strap with a Velcro fastener. The participant will sit on a tall chair with a strap around the lower leg 10 cm above the ankle joint, and the hip and knee joint angles will be positioned at 90°. The distance from the knee joint to the strap around the ankle will be measured with a tape measure. This measure will be used for the calculation of torque (i.e. force [N] distance [m]). The maximum voluntary contraction will be assessed during an isometric knee extension. Participants will be asked to perform three maximum voluntary contractions trials for each leg. The contractions will last up to five seconds each, with a rest period of one minute between each trial. The force data will be stored on a portable computer. The best performance of the three trials will be considered as the maximum torque for each side.Spatio-Temporal Gait Parameters: Measures of stride dynamics and gait variability have been shown to identify fallers in older adults with gait limitations and those with a history of falls [41, 42]. Assessment of walking speed, stride length, stride width and double limb support will be performed with the use of the GaitRite® system (CIR System, Inc, Harverton PA) instrumented walkway system (active length of the mat: 8.75 m). Participants will be asked to start from a point 3 m in front of the mat and will stop on a point 3 m behind the mat. Approximately 10 strides per participant are required to achieve reliable mean estimates of spatio-temporal gait parameters including velocity, stride and step length, and step and single support time [43, 44]. Therefore, seven walks will be recorded to allow sufficient data to be collected. Multiple practice trials will be given until participants feel comfortable and will be walking with consistent velocity. This will be followed by seven testing trials which will allow sufficient number of strides to be recorded. Participants who use a gait aid for indoors walking will be allowed to use it during the tests. Participants will be wearing flat shoes during the test.The following questionnaires will be used to evaluate health related quality of life measures and psychological or psychosocial measures:*The Short Form (12) Health Survey Version 2 (SF-12v2™)* is a 12-item questionnaire which evaluates the individual health status over eight domains including vitality, physical functioning, bodily pain, general health perceptions, physical role functioning, emotional role functioning, social role functioning, and mental health [45]. The SF-12v2*™* has been given preference for use among older people (compared with other longer versions of measures of quality of life such as SF-36) because of its brevity. [46]. Most questions use a five-value response option (all of the time, most of the time, some of the time, a little of the time, and none of the time) and some a three-value response option (yes, limited a lot, limited a little or not limited at all). Physical and Mental Health Composite Scores (PCS & MCS) are computed using the scores of twelve questions and range from 0 to 100, where a zero score indicates the lowest level of health measured by the scales and 100 indicates the highest level of health [45].*The Incidental And Planned Activity Questionnaire (IPAQ)* for older people will be used to assess the physical activity level of the participants [47]. The IPAQ is a self-report questionnaire that covers the frequency and duration of several levels of planned and incidental physical activity in older people. Planned activities (6-items) include planned exercise or walks whereas incidental physical activities (6-items) include day-to-day activities like housework or gardening. Total hours per week spent in both incidental and planned physical activity will be obtained by multiplying frequency scores and duration scores. Summation of the incidental and planned physical activity hours per week will also provide a total activity score. The IPAQ has been shown to have good test-retest reliability and concurrent and face validity [47]. The IPAQ is relatively short and easy to complete by older individuals and has been used previously in studies of fall risk factors and prevention programs in older people [48–50].*The falls efficacy scale (Short FES-I)* questionnaire will be used to record fear of falling [51]. The FES-I consists of 7 items using a Likert scale that assesses the participant’s level of concern regarding the possibility of falling when performing certain daily activities. Items are scored from *1* = not concerned at all to *4* = very concerned. The total score ranges from 7 (not concerned) to 28 (Severely concerned to match to the description on score 7) where higher scores are associated to a greater fear of falling [51]. The test–retest reliability of the Short FES-I is good (*r* = 0.92) [51].*Social activity participation* will be measured with a 10-item questionnaire which was derived from a measure of social functioning [52] and has been previously used to measure social participation in people who had repeated falls [53]. Participants will be asked to record the number of times in the previous two weeks that they have participated in 10 categories of social activities including: gone to church, visiting friends and family, gone to concerts, plays, or sporting events; gone to fairs, museums or exhibits; and attended meetings, appointments, classes/lectures. Questions use a five-value response option (less than once/week, once/week, twice/week, 3–6 times/week and every day). A summary score of social participation will be calculated as the total number of times in which the participant undertook any of the 10 activity categories during the period in question (two weeks). Higher scores are associated with a higher level of social activity.Physical self-perceptions will be measured using the *Physical Self-Description Questionnaire (PSDQ) – Short Form* [54]. The PDSQ is a 40-item questionnaire scored from 1 (false) to 6 (true) and consists of 11 factors: Health, Coordination, Activity, Body fat, Sport, Global Physical, Appearance, Strength, Flexibility, Endurance and Global esteem. The PDSQ has been shown to have good test-retest stability over a 3 month period (*r* = .81 to .94) strong factorial structure and discriminant and convergent validity [54].*Falls and physical activity calendar*—Participants will be requested to record any falls and physical activity or exercise experienced using a monthly calendar for 12 months from the baseline assessment. At the end of each month the calendar will be returned to the researchers in a reply paid envelope. If the calendar is not returned within two weeks of the end of a month, the participant will be followed up with a phone call. For this study, a fall will be defined as “inadvertently coming to rest on the ground, floor or other lower level, excluding intentional change in position to rest in furniture, wall or other objects” [14] and this definition will be explained to the participant to make sure they fill in the calendars accurately.

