Safety and adverse effects will be measured by the number of falls incidents that occur during exercise sessions, and will be recorded via an incident report form (treatment needed post-incident and related lesions or injuries). The circumstances surrounding the fall (e.g. muscle fatigue, dizziness) will be recorded. EPIG participants will be also asked in the following session (48 h) to report if they experienced any uncomfortable delayed muscle soreness or fatigue post-exercise that limited them from doing their daily tasks such as ascending and descending stairs, rising from a chair, and carrying shopping bags. The following question will be used: “Did you experience any muscle soreness after the session that limited you from doing your normal daily activities such as carrying shopping bags, rising from a chair or putting a t-shirt on?”. If they answer “yes” the muscle soreness event will be recorded on the participant’s spreadsheet diary.

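### As described, the safety measure counts falls and their injuries only during exercise sessions, so it gives no between-arm account of fall injuries over the 12 months

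*Protocol article*

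**What the plan says.** The protocol article describes two records of falls.

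- **In-session record (Feasibility).** "Safety and adverse effects will be measured by the number of falls incidents that occur during exercise sessions". These incidents "will be recorded via an incident report form (treatment needed post-incident and related lesions or injuries"), and the circumstances of the fall are noted. The same paragraph adds a question on limiting muscle soreness, asked of exercise-group participants only.
- **Calendar (Secondary measures).** All participants are asked to "record any falls and physical activity or exercise experienced using a monthly calendar for 12 months from the baseline assessment". The article gives the fall definition, monthly return by reply-paid post, and one trigger for contact: "If the calendar is not returned within two weeks of the end of a month, the participant will be followed up with a phone call". It names no item on injury or care, and no contact after a calendar that reports a fall.

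A third, indirect source is the attendance diary (Feasibility), which notes why a session was missed. Participants who miss two sessions in a row without contact are phoned.

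The Background gives the rates used below: "About one third of people aged 65 years or older fall at least once a year", and "20 % of those who fall experience injuries requiring medical attention". The statistical analysis section says the trial is not powered for falls.

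**The concern.** The only record described as holding injury and treatment is tied to the exercise sessions. Control participants have social meetings and no exercise sessions, so the measure cannot produce a control-arm figure. Exercise-group participants are covered for a small part of the year.

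The programme is meant to make people at some risk of falling more active, and recruits those "who have had one or more falls in the previous 12 months or who are concerned about having a fall will be recruited". Whether falls in daily life do harm, and whether that differs between arms, is a natural safety question. The trial already collects the falls themselves in both arms for 12 months. What the article does not describe is any record of their consequence. If that is not captured when the calendar is filled in, it can be recovered later only from memory. The safety statement in the final report would then rest on in-session incidents in one arm.

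**Working it through.** The plan states no expected number of fall injuries, so there is no figure of its own to reproduce. The check has two parts: which falls each record covers, and how many injuries could be involved.

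**Coverage as described**

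| Record | Arms | Period | Injury or care recorded |
|---|---|---|---|
| Incident form | Exercise only | In sessions, 18 weeks | Yes |
| Monthly calendar | Both | 12 months | None described |
| Attendance diary | Both | 18 weeks | Only if given as the reason for absence |

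**Inputs**
- Participants: 120, 60 per group (Sample size).
- Proportion falling in a year: 1/3. Proportion of fallers with a medically attended injury: 0.20 (both Background, general rates).
- Sessions: 2 per week × 18 weeks = 36, each 1 to 1.5 h (text under Fig. 1), so 36 to 54 h. The 50 expected hours under Fidelity monitoring lie within this range.
- Hours in a year: 365 × 24 = 8,760. Waking hours at 16 per day (assumption): 5,840.

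**Expected injured participants** = N × P(fall) × P(medically attended injury given a fall)
- All 120: 120 × 1/3 × 0.20 = 8, or 4 per arm.
- After the plan's 20 % dropout, 96 remain: 96 × 1/3 × 0.20 = 6.4.
- If half the sample fell (assumption, since entry selects for past falls or concern): 120 × 0.50 × 0.20 = 12.

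**Share of the exercise arm's injuries that occur in sessions.** With session hours h, total hours T and an hourly risk in sessions r times that elsewhere, share = hr / (T − h + hr). Expected number of the 8 reaching the incident form = 4 × share.

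| h | T | r | Share of exercise arm | Of the 8 |
|---|---|---|---|---|
| 36 | 8,760 | 1 | 0.41 % | 0.02 |
| 54 | 5,840 | 1 | 0.92 % | 0.04 |
| 36 | 8,760 | 10 | 4.0 % | 0.16 |
| 54 | 5,840 | 10 | 8.5 % | 0.34 |
| 54 | 5,840 | 20 | 15.7 % | 0.63 |

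The multipliers 10 and 20 are assumptions. Even in the last row the form is expected to see fewer than one of the 8. In the control arm it sees none.

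**Attendance diary, upper bound.** If injuries are spread evenly over the year, 18/52 × 8 = 2.8 arise during the intervention weeks. All would be caught only if each led to a missed session and was given as the reason.

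**The case against.** The strongest objection is that this is a journal article and the calendar form is not shown. The article lists no form fields, not even the date of a fall, and such detail commonly sits in the full protocol. This stands against one tempting reading. A reader might infer that the calendar omits injury, so that nearly all fall injuries will go uncounted. The documents do not support that: the article is silent on the form's content, and silence about a call after a reported fall does not exclude one. It does not remove the point about the safety measure, whose restriction to exercise sessions is stated outright.

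Second, injurious falls are neither an aim nor an outcome of this trial. The Background cites injury as motivation, while the aims concern fall risk, functional, physiological and psychosocial benefit, and whether benefits last. This also stands, so no planned efficacy analysis fails. The point concerns the account of harm.

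Third, the numbers are small. The 8 carries general rates for people aged 65 or older into a sample aged 60 to 90 selected for past falls or concern, and the plan itself predicts no such count. With 8 events and 60 per arm, a 7 to 1 split gives a two-sided Fisher p of 0.06; only 8 to 0 falls below 0.05. A test would therefore tell little. But the proposal is a descriptive count by arm, so the lack of power for falls does not answer it.

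Fourth, the diary may bring some injuries to light in either arm. It may, but unsystematically, and only during the 18 weeks.

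**Conclusion.** The point holds in this form: the stated safety measure is limited to exercise sessions, and the article describes no other systematic record of fall injury. As described, the trial can report falls by arm over 12 months but not injurious or medically attended falls by arm.

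Under the Background's rates, about 8 of 120 participants would be affected (6.4 to 12 over the variations tried), with fewer than one expected to reach the incident form. These figures rest on transferring general-population rates and on assumed relative hourly risks, so they illustrate the size of the gap and are not a forecast. That the calendar lacks injury items remains unconfirmed until the form is checked. This is a worthwhile, inexpensive improvement to the safety reporting. It does not threaten the primary analysis.

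**What to change.** 1. In Feasibility, extend the safety measure from falls in exercise sessions to all falls in both arms over the 12 calendar months, keeping the in-session incident form.
2. Check the calendar form. If they are not already there, add to each fall entry its date and two yes/no boxes: injured, and medical attention sought.
3. Use the existing phone contact to confirm entries with either box ticked, as well as to chase unreturned calendars.
4. Report injurious falls and medically attended falls by arm over 12 months, as descriptive counts alongside in-session incidents, with the number of calendar months returned in each arm.

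The cost is slightly more for participants to fill in and a few extra calls, on the illustrative figures about 8 for medically attended injuries plus those for lesser injuries. No visit or procedure is added. If the form already holds these items, only the wording of the safety measure and the reporting need to change.

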
### Qualitative data

Participants allocated to EPIG will be interviewed by an experienced qualitative researcher at the end of the intervention period (18 weeks). An interview guide (see Additional file 1 – Interview Guide) will explore the participant’s experience with the project including reasons to volunteer to the project and their experiences with the training program (staff supervision, frequency, duration, progression of exercises, level of difficulty, changes to their life in general and general level of satisfaction). Only participants assigned to the exercise intervention group will be interviewed. In interviewing these participants, we aim to be able to identify the positive and negative elements of the exercise park program perceived by the participants, as well as the main participation barriers which can impact on the adherence and acceptability of the intervention. The interviews will be conducted on an individual basis by a researcher independent to the intervention. All interviews will be digitally recorded and transcribed verbatim. The interviews will be analysed using a thematic analysis approach [55]. Data will first be coded to identify and label text to the participants experience of the exercise park using both an inductive and deductive approach. These codes will then be placed into overarching themes. Inter-rater reliability will be examined by an independent coder on all of the themes and subthemes by reviewing a random sample of 10 % of all the excerpts relating to each theme and sub-theme with any differences in coding discussed between the coders [56].

